**Fig. 1 Fig1:**
[figure not shown]
Study flow chart. MPE, malignant pleural effusion

### Sample size

This study will enrol 158 patients to detect a 5% reintervention rate in optimised IPC vs 25% reintervention rate in VATS (based on previous studies [13, 22, 23]). The sample size calculation was carried out using an anticipated Fishers exact test to compare these proportions in each of the two groups. With a 5% significance level and a power of approximately 90%, we would need 75 patients per group with an additional 4 patients per group to allow for dropouts (5% anticipated) giving a total of 158 patients. Withdrawal or loss to follow-up only occurred in 4.8% (7/146) patients in our previous AMPLE-1 trial of MPE [22].

### Randomisation and blinding

Participants will be randomly assigned (1:1) to either IPC (with talc if suitable) or VATS pleurodesis. Randomisation will include minimisation for (i) cancer type (mesothelioma vs non-mesothelioma); (ii) previous pleurodesis (*vs* not); and (iii) trapped lung, if known (*vs* not known). The nature of the intervention means that investigators and patients cannot be blinded to the treatment arms. The National Health and Medical Research Council Clinical Trials Centre, Sydney, Australia, provides the randomisation setup via their automated telephone-based interactive voice response services. Where possible, data analysts will be blinded for analysis of the outcomes although the very different profiles of treatment outcomes of the allocated treatments will make complete blinding difficult.

### Data management and safety

Data will be entered into a secure database and a system of data validation checks will be implemented and applied. The accuracy of the data will be verified through data monitoring and comparison to source documents. Data entered will be checked by a second staff to ensure accuracy.

All physical documentation will be stored in a secure environment in line with the Australian Code for the Responsible Conduct of Research for clinical trials and local policy guidelines for research data archiving. All procedures for the handling and analysis of data will be conducted using GCP ICH guidelines, the National Statement on Ethical Conduct in Human Research (2007)—*Updated May 2015*, and local policies and procedures for the handling and analysis of data.

### Statistical plan

Data will be analysed on an intention-to-treat basis and per protocol basis. The primary outcome will be analysed using a Fisher’s exact test for comparing two proportions and subsequent logistic regression analyses allowing adjustments for minimisation variables. A secondary analysis of the primary outcome will use a competing risks time to event analysis with the competing risk of death. For the secondary outcomes, e.g., hospital days and VAS measurements, the difference between the groups will initially be examined using two sample *t*-tests and further adjustments will be made for minimisation variables. Subsequent analyses will consider the repeated VAS scores measured on the same patient and missing VAS scores (assuming that missing scores are missing at random) and will include a time by treatment interaction term along with random intercepts and time effects as appropriate. An interim analysis is planned after the recruitment and follow-up of 60–80 participants.

The research team will document as accurately as possible the reasons for any non-completion or missing data, thereby minimising truly absent data. The expected dropout rate from patient death has been factored into the power calculation and is based on survival figures and previous studies.

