
### Participant timeline

Baseline data will be collected once informed consent has been obtained. Data collected will include demographics, ASA, ECOG performance status, questionnaires (VAS breathlessness, VAS QoL, VAS pain, EQ-5D-5L), comorbidities, malignancy type, stage and treatment, baseline bloods (full blood picture, albumin, lactate dehydrogenase, C-reactive protein), baseline CXR findings, baseline ultrasound thorax and pleural effusion data including laboratory results and previous interventions.

The assigned intervention will be scheduled to occur within 2 weeks of randomisation. Participants will be followed up between day 7 and 10 post-procedure, monthly to 6 months, at 9 months, and at 12 months or death if sooner (Table 1, Fig. 1). There will be a visit ‘window’ initially of ±3 days surrounding the early visits. Later visit dates will have a larger visit window.

**Table 1 Tab1:** Schedule of treatment for each visit and follow-up procedures

	Study period								
	Pre-procedure		Post-procedure						
	Enrolment	Within 2/52	Days post-procedure				Months		
Timepoint	***T-1***	***T0***	***D1***	***Discharge***	***D7-10***	***D28***	***2–6***	***9***	***12***

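### The t-tests and adjusted comparisons of VAS and EQ-5D-5L use no baseline score although one is collected, and how baseline enters the repeated-measures VAS model is not stated

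*Protocol article*

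**What the plan says.** The Statistical plan section of the protocol article gives three layers of analysis for secondary outcomes, with hospital days and VAS named as examples.

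1. A two-sample t-test.
2. An adjusted comparison: "further adjustments will be made for minimisation variables".
3. For the repeated VAS scores, a model that "will include a time by treatment interaction term along with random intercepts and time effects as appropriate", with missing scores assumed missing at random.

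The Randomisation and blinding section lists the minimisation variables as cancer type, previous pleurodesis and trapped lung if known.

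The Participant timeline section includes among the baseline data "questionnaires (VAS breathlessness, VAS QoL, VAS pain, EQ-5D-5L", and Table 1 schedules these questionnaires at the enrolment visit, before the procedure.

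No layer names a baseline score as a covariate, and no change-from-baseline analysis is stated. EQ-5D-5L is not named in the Statistical plan; it falls only under the general wording for secondary outcomes.

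**The concern.** The baseline value of a symptom or quality-of-life score is commonly among the better predictors of the later value of the same score. An analysis that has it and leaves it out gives a wider confidence interval than it needs to.

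This matters more than usual here because the trial is sized only for the re-intervention rate. No VAS or quality-of-life outcome has its own SD, target difference or power figure, and deaths will thin the numbers scored at later visits. Precision on breathlessness, whose relief the Introduction calls a key goal of management, has to come from the analysis.

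This is not detail simply left to an analysis plan: the article names both the test and an adjustment set, and that set contains no baseline score.

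**Working it through.** **The plan's own figure.** The only sample-size figure is for the primary outcome: "detect a 5% reintervention rate in optimised IPC vs 25% reintervention rate in VATS", and "With a 5% significance level and a power of approximately 90%, we would need 75 patients per group". It reproduces.

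- Normal approximation, two-sided 5% (sidedness assumed), mean proportion 0.15: n = [1.96·√(2·0.15·0.85) + 1.2816·√(0.05·0.95 + 0.25·0.75)]² / 0.20² = 64.9, so 65 per group.
- With the continuity correction: (64.9/4)·[1 + √(1 + 4/(64.9·0.20))]² = 74.5, so 75 per group.
- Exact enumeration of Fisher's test at 75 per group gives power 92.8%, at least the stated level.
- Dropout: 75/0.95 = 78.9, so 79 per group and 158 in total.

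Nothing below changes this figure.

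**Inputs for the point.** 75 per group (150 in total), 1:1 allocation, and r, the within-arm correlation between the baseline and follow-up score. The documents do not give r, so it is assumed over 0.2 to 0.6. Baseline and follow-up SDs are taken as equal, and all 150 participants as scored.

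**Formulas.** Variance of the treatment difference relative to a follow-up-only t-test:

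- Baseline as covariate (ANCOVA): 1 − r².
- Baseline as an unconstrained response, effect read from the time-by-treatment contrast (a change score): 2(1 − r).
- Equivalent number analysed without baseline: 150/(1 − r²).
- Difference detectable at 80% power, in SD units: (1.96 + 0.842)·√(2·(1 − r²)/75). Without baseline adjustment (factor 1) this is 0.457.

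| Assumed r | ANCOVA 1 − r² | Variance saved | Change score 2(1 − r) | Equivalent n | Detectable difference (SD) | Power for 0.457 SD |
|---|---|---|---|---|---|---|
| 0.2 | 0.96 | 4% | 1.60 | 156 | 0.448 | 81.6% |
| 0.3 | 0.91 | 9% | 1.40 | 165 | 0.436 | 83.6% |
| 0.5 | 0.75 | 25% | 1.00 | 200 | 0.396 | 89.9% |
| 0.6 | 0.64 | 36% | 0.80 | 234 | 0.366 | 93.8% |

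The last three columns refer to the ANCOVA.

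**Reading the mixed model.** The stated terms fit at least four treatments of the baseline score.

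- Left out: follow-up-only precision, factor 1.
- Covariate: about 1 − r².
- Response with one baseline mean common to both arms: about 1 − r².
- Response with a separate baseline mean in each arm: 2(1 − r).

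The last exceeds the ANCOVA factor by 2(1 − r) − (1 − r²) = (1 − r)², so it never beats ANCOVA. If r is below 0.5 it is also less precise than ignoring baseline altogether.

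**The case against.** The strongest reply has four parts.

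- **The text does not exclude baseline adjustment.** It does not say that the minimisation variables are the only covariates, and a fuller list may sit in an analysis plan that is not shown. This stands as a limit: one cannot say that baseline will not be used. It does not remove the point, because the named set is a stated choice that can be improved.
- **The repeated-measures VAS model may already use the enrolment score as one of the repeated scores.** This also stands. A reader might infer that precision is thrown away on all patient-reported outcomes, or that chance baseline imbalance goes uncorrected throughout. The documents do not support either. With a common baseline mean, that model has about ANCOVA precision; even unconstrained, its interaction contrast removes baseline differences. What remains is that the article does not say which applies. The model is also described for VAS, so it does not clearly cover EQ-5D-5L.
- **The size is assumed.** This stands. Breathlessness at enrolment is scored in symptomatic patients before fluid is removed in both arms, so r could be low and the gain small. The comparator is a follow-up-only analysis with no one lost to death, not the planned mixed model.
- **Some premises are softer than they look.** Table 1 puts questionnaires and randomisation in the same enrolment column without giving their order, so it is safe to say only that the scores precede the procedure. Nothing guarantees that every participant's baseline score is complete.

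A reader might also infer bias. Under randomisation, omitting a baseline covariate does not bias the comparison, and chance imbalance is already reflected in the confidence interval.

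**Conclusion.** The point holds as a matter of precision on secondary outcomes. As written, the t-tests and the comparisons adjusted for minimisation variables leave out a prognostic covariate that the trial collects. For EQ-5D-5L this follows from the general wording only.

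The loss is real for any r other than zero, but its size cannot be fixed from the documents. It is slight at r = 0.2 and substantial at 0.5 or above. For the mixed model, the finding is that the wording is open between versions that recover the precision and one that can do worse than ignoring baseline; it is not that baseline is unused.

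The primary outcome, its test and the sample size are untouched. The change is worth making but is not critical to the trial's main conclusion.

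**What to change.** - Replace the t-tests and the minimisation-only adjustment for the VAS scores and EQ-5D-5L by ANCOVA, with the baseline value of the same score and the three minimisation variables as covariates. An unadjusted t-test can stay as a description. Hospital days has no baseline value and is not affected.
- In the repeated-measures model, state one of two options: baseline as a covariate with a baseline-by-time term, or baseline as a response with a common mean across arms. Include the minimisation variables as fixed effects.
- Say whether the same model applies to EQ-5D-5L.
- Confirm that the enrolment questionnaires are completed before allocation is known, since the common-mean option relies on this and the trial is open-label.

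The cost is a sentence or two of analysis wording, with no new data, visits or participants. It should be settled before outcome data are examined by arm, including at the planned interim analysis, so that the covariate choice cannot be questioned later.

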### Ethics

The trial has been approved by an ethics committee for all sites (see declarations). The investigators will receive approval from the ethics committee for any amendment to the protocol and ensure it is signed by any patient subsequently entering the trial and those currently in the study, if affected by the amendment.

### Trial monitoring and oversight

The trial steering committee (TSC) will be responsible for the supervision of the trial in all its aspects, including completion of the trial to clinical and ethical standards. Members of the TSC include the principal investigator, selected investigators from each site, external independent members, a consumer representative, and the trial coordinator.

The data safety and monitoring board (DSMB) will ensure the safety of study participants through monitoring of ethical conduct of the study and adverse events and consider new data (recently published studies) that may determine the validity of study continuation. The DSMB includes an independent chairperson and other independent members, one of whom is a statistician.

### Adverse event reporting and harms

Although both arms of this study involve procedures that are standard of care, participants will be carefully monitored for the development of adverse events, which will be documented according to standard “Adverse Event Reporting”. Any serious adverse events, whether related to the intervention or not, will be reported, documented, and reported to the DSMB. Adverse events will be followed up until resolution or documented as not resolved on the adverse event log at study completion.

All deaths, anticipated or unanticipated, will be discussed with the DSMB. The committee determines whether significant benefits or risks have been uncovered which may have an impact on the feasibility and/or ethical conduct of the study. The DSMB will also help to ensure the scientific integrity of the study by reviewing the quality of the data it uses to make its decisions.

### Plans for dissemination

It is expected that the study results will be published in a peer-reviewed journal. Presentations at national and international conferences are anticipated.

## Discussion

IPC and VATS are both well-established treatments for MPE, but the choice of procedure is often dictated by clinician bias and available resources. The results of this study will provide the first objective evidence-based guidance on which treatment would be the best for patients who are suitable for both interventions.

## Trial status

Protocol version: Version 3.00/4.02.19

Date recruitment began: 23 April 2019

Estimated recruitment completion date: 31 December 2024

## Data Availability

The research team at the lead site will have access to the final trial dataset. Supporting data including standard operating procedures, details of data management procedures, case report forms, and datasets generated and/or analysed during the current study will be available to the scientific community with as few restrictions as possible, while retaining exclusive use until publication of major outcomes. Data requests from qualified researchers should be made to [name] ([contact]).

## Abbreviations

ASA: American Society of Anaesthesiologists score
CXR: Chest x-ray
DSMB: Data and Safety Monitoring Board
ECOG: Eastern Cooperative Oncology Group
IPC: Indwelling pleural catheter
MPE: Malignant pleural effusions
QoL: Quality of life
SAE: Serious adverse event
TSC: Trial Steering Committee
VAS: Visual analogue scale
VATS: Video-assisted thoracoscopic surgery
